### Randomisation and blinding

The study was designed as a single-blinded RCT. Participants will be randomly assigned into three groups by two trained assessors who will not participate in the intervention. A sequence number will be generated by SPSS 25.0 under the ratio of 1:1:1. The numbers will be placed in a sealed envelope and randomly distributed to the participants. The instructors in each group will be blinded to the group allocation, including the control group, and the instructors should not know each other. This study will be unable to blind participants because of the differences in the intervention methods to be used in the three groups.

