### Sample size calculation

Sample size estimation was conducted using G*Power V.3.1 (Franz Faul, Universitat Kiel, Germany). The purpose of this study is to examine the effects of HIIT on the major cognitive functions of MA dependents. However, informed preliminary data and empirical evidence on the effects of HIIT are lacking. Thus, we estimated the effect size in these power calculations using an estimated sample from published studies that compared the effects of HIIT and continuous training on cognitive function in healthy adults [65]. Specifically, we used the values of some variables within the ANOVA framework in this essay to obtain an effect size of 0.28 through the *t* test. Then, according to the *F*-test at *α* = 0.05 and power = 0.95, we obtained the required sample size of 223 subjects. The final average enrolment number with an anticipated 10% attrition rate is 240 (80 in each group) for the study to detect the difference in the cognitive outcomes between HIIT and MICT relative to the control group.

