### Statistical analysis

SPSS 25.0 will be used for statistical analysis. The descriptive outcomes will be displayed as mean ± standard deviation. The *F*-test will be applied to test the continuous variables, and the chi-square test will be used to test the classification variables. For the Stroop test, reaction time (congruent and incongruent) and accuracy (congruent and incongruent) will be analysed using 2 (time points: pre-test vs. post-test) × 3 (groups: HIIT vs. MICT vs. control) repeated-measures ANOVA. Other data will also be analysed using repeated-measures ANOVA. All post hoc tests will be corrected by Bonferroni for multiple comparisons. Intention-to-treat analysis will be used to process the missing data. The linear mixed model method will be applied to analyse all continuous variables with random missing values. The magnitude of the difference between fitness levels will be assessed by Hedges’ *g* [28], and the magnitude will be classified as small (0.2 < ES < 0.5), moderate (0.5 < ES < 0.8) or large (ES > 0.8). The significance level will be set at *p* < 0.05 for all analyses.

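### The sample-size figures 223, 10% and 240 do not follow from one another or from a three-group F-test at f = 0.28, which needs 201; the metric of the 0.28 is not stated

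*Protocol article*

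**What the plan says.** All the figures are in the protocol article, section Sample size calculation. The authors report having no preliminary data on HIIT in this population. They take values from a published comparison of HIIT with continuous training in healthy adults "to obtain an effect size of 0.28 through the" t test. They then move to an F-test with alpha 0.05 and power 0.95, and report that "we obtained the required sample size of 223 subjects". The next sentence reads: "The final average enrolment number with an anticipated 10% attrition rate is 240 (80 in each group").

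The section does not name the metric of the 0.28, the type of F-test, the numerator degrees of freedom, the number of measurements or a correlation between them.

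Two other sections fix the design. Under Randomisation and blinding there are three groups, and "A sequence number will be generated by SPSS 25.0 under the ratio of 1:1:1". Under Statistical analysis, the Stroop measures go into a design with two time points and three groups ("groups: HIIT vs. MICT vs. control) repeated-measures ANOVA").

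**The concern.** This paragraph is the only justification for enrolling 240 people, and it has three faults.

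- **Required number.** The 223 is presented as the output of an F-test with stated inputs, but a three-group F-test with those inputs does not return it.
- **Attrition step.** Allowing for 10% loss should leave at least the required number. Here it leaves fewer.
- **Effect-size metric.** A t test ordinarily yields a standardised mean difference d, while the G*Power F-test for ANOVA takes f. For two equal groups f = d/2, so the same 0.28 means quite different effects on the two scales.

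The first two faults are in the reported arithmetic. The third decides whether the claimed power is real, and the text does not settle it.

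**Working it through.** **Inputs**

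| Input | Value | Source |
|---|---|---|
| Groups, allocation | 3, 1:1:1 | Randomisation and blinding |
| Effect size | 0.28, metric not named; read first as f | Sample size calculation |
| Alpha, power | 0.05, 0.95 | Sample size calculation |
| Stated requirement | 223 | Sample size calculation |
| Attrition, enrolment | 10%, 240 | Sample size calculation |

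**Formula.** For a fixed-effects one-way ANOVA with k groups and total N, the noncentrality is λ = N·f². Power is the probability that a noncentral F with df1 and N − k degrees of freedom exceeds the central 95% point.

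**Step 1. Try to reproduce 223.** With f = 0.28:

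- Numerator df 3, as for a four-group main effect: N = 222 gives 0.949 and N = 223 gives 0.950. This matches exactly.
- Numerator df 2 with attrition included: 201/0.9 = 223.3. This matches after rounding down.
- Repeated-measures versions (2 or 3 measurements, correlations 0 to 0.9): the between-group test needs 69 to 191 and the group-by-time test 11 to 102. None gives 223.
- ANCOVA with one to three covariates needs 201.

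A slightly different effect, f = 0.265 with df 2, also gives 223, but that is not the stated value.

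**Step 2. The test as described.** k = 3, df1 = 2:

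- N = 200: power 0.94999, just short.
- N = 201: λ = 201 × 0.0784 = 15.76, power 0.951.

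The requirement is 201, or 67 per arm. Allowing for 10% loss gives 201/0.9 = 223.3, so 224 enrolled.

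**Step 3. From 223 to 240.** This needs no assumption about the test or the metric:

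- 223/0.9 = 247.8, so 248 enrolled. Even the cruder 223 × 1.1 = 245.3 gives 246.
- 240 × 0.9 = 216, which is 7 below 223.
- 1 − 223/240 = 7.1%, the largest loss that 240 can absorb if 223 is required.

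**Step 4. Power with 216 evaluable, f = 0.28.**

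- df1 = 2: λ = 216 × 0.0784 = 16.93, power 0.964.
- df1 = 3: power 0.943.

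**Step 5. If 0.28 is a d, one-way comparison of single measurements.**

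| Conversion | f | Power at 216 | N for 0.95 |
|---|---|---|---|
| Two-group rule, d/2 | 0.140 | 0.43 | 791 |
| Three means 0, 0, 0.28 SD | 0.28·√2/3 = 0.132 | 0.39 | 890 |
| Three means 0, 0.14, 0.28 SD | 0.28/√6 = 0.114 | 0.30 | 1,185 |

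**Step 6. The same d in a pre/post analysis.** For a group test on change scores, f is divided by √(2(1 − ρ)), where ρ is the pre/post correlation (an assumption; the article gives none). Across the three conversions, power at 216 is:

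- ρ = 0.5: 0.30 to 0.43, as in step 5
- ρ = 0.7: 0.47 to 0.65
- ρ = 0.8: 0.65 to 0.83

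Below ρ = 0.5 it is lower than in step 5; at ρ = 0.3 it is 0.22 to 0.32.

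**The case against.** The strongest defence is that nothing of substance is lost. If 223 is 201/0.9, it uses only stated inputs and already contains the attrition. The 240 is then a generous rounding to 80 per arm, and the fault is one of wording. The shortfall of 7 is measured against a 223 that is itself larger than a three-group test needs. That 223 does not divide by three is no error either, since enrolment is set at 240. All of this stands, and it bears on how serious the point is. It does not rescue the paragraph, which presents 223 as the number before attrition and then applies attrition in a step that does not work.

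A reader might infer that the trial misses its 0.95 power. The documents do not support that. With f = 0.28 and 216 evaluable, power is 0.964, and even numerator df 3 gives 0.943.

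A reader might also infer that 0.28 is a d and that the true power is 0.30 to 0.43. That is not established. The mention of a t test suggests d, but the same sentence places the source values in an ANOVA framework, and the cited study is not at hand. The match to 223 with 0.28 entered as f shows at most what was typed into the program, not what the source value was. The 0.30 to 0.43 range also assumes single measurements, whereas the Stroop plan is pre/post.

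**Conclusion.** The point holds as an inconsistency in the stated calculation. With f = 0.28 and three groups the requirement is 201, not 223. The step from 223 to 240 contradicts the stated 10% loss on any reading: 248 would be needed, and 240 leaves 216. The text does not show whether attrition was counted twice or the numerator df was wrong.

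The effect on power depends on the metric. If 0.28 is f, there is none to worry about: 216 evaluable gives 0.964 for the omnibus test. If an unconverted d was entered as f, the claimed 0.95 fails in every case computed in steps 5 and 6. How far it falls depends on the pattern of means, the analysis and the pre/post correlation. The d reading is conditional and has to be settled from the source of the 0.28.

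**What to change.** Keep enrolment at 240 and restate the paragraph: omnibus F-test, three groups, numerator df 2, f = 0.28, alpha 0.05 and power 0.95 give 201 (67 per arm), or 224 after 10% attrition; 240 enrolled leaves 216 evaluable and omnibus power of 0.96.

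Confirm from the source calculation that 0.28 is f, and say so. If it is d, convert it to f for three groups, stating the assumed pattern of means, and restate the power at 216 for the planned analysis with its assumed correlation. No replacement power figure should be written in until those assumptions are stated.

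The cost is protocol wording and a check of the source calculation, with no extra participants. The stated power may turn out less favourable. The article describes recruitment as ongoing, so on that status the correction could still be made before results are known.

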### Intervention

#### HIIT group

The HIIT group will undergo three interventions per week for 6 whole months on a treadmill. Total exercise time is 24 min, including 3 min of warm-up with low intensity (walking or jogging), 18 min of high-intensity training and moderate-intensity intervals and 3 min of relaxation (walking or jogging). The 18-min HIIT process will consist of six groups of 2-min high-intensity exercises and 1-min moderate-intensity intervals. Training will be conducted under the supervision of professional instructors. During the supervised intervention, heart rate (HR) will be recorded using a Polar HR monitor (model FT4; Polar Electro, Finland) to encourage or ensure that an appropriate exercise intensity is maintained according to their measured maximum HR. In addition, each subject will be able to observe their exercise intensity and real-time HR from a 6 × 3 m^2^ projector curtain.

Different parts of the intervention will have different exercise intensities. Warm-up will be 50–65% of the maximum HR, and the 2-min high-intensity training will be 80–90%. The 1-min moderate intermittent exercise will be 70–80% of the maximum HR. The target intensity of relaxation will be 50–65% of the maximum HR in theory [75]. Exercise intensity will be controlled by regulating the speed of the treadmill. All interventions will be implemented in the afternoon. Except for the different intervention parts, the participants were advised to carry out their daily rehabilitation staying the same carrying out by the administrators and will be instructed to remain their usual lifestyle (such as diet and medication).

#### MICT group

The MICT protocol will consist of TC rehabilitation exercises and self-designed body–mind exercises. Twenty-four-style TC movements, including ‘part the wild horse’s mane on both sides, hold the lute, forearm on both sides, grasp the bird’s tail, brush knee and twist step on both sides and golden rooster standing on one leg’ will be reserved in the TC rehabilitation exercise, and the entire exercise duration will be nearly 4–5 min. The self-designed body–mind intervention will consist of nine forms of exercise, which are tailored to the physical and mental characteristics of illicit drug users. These movements combine TC, Qigong and Yoga and emphasise dynamic postural control and body weight shift stepping with lateral–medial and anterior–posterior movements, body symmetry pulling across up–down and left–right axes and hand-eye coordination movement. The duration of each session is 1 h. The frequency of intervention in the MICT group will be the same as those of the HIIT and control groups. Exercise intensity will be achieved by adjusting the movement range and squat height under the guidance of professional instructors.

#### Control group

The control group will be instructed to continue their normal intervention, including relevant health education, as well as their daily activities, such as reading books and watching news. The intervention in this group will be conducted under the supervision of an administrator from the rehabilitation centre. The subjects and the administrator should not know each other.

### Incremental exercise test

The primary purpose of this test is to obtain the maximum HR of the HIIT group to minimise or avoid the risk that may occur during the formal intervention. Participants will be tested on a power bike following the cardiopulmonary test guidelines of the American Heart Association [8] after knowing the procedure of the experiment. Borg 6–20 scale will be used to measure motion perception every 2 min [14]. The test will stop when the subjects reach the maximum voluntary fatigue index of 18–20 as determined by the scale, that is, when the participants are unable to reach the established rhythm (< 5 RPM) for 5 s or they show signs of extreme fatigue.

### Adverse events

The safety of patients will be monitored during the intervention and their daily life. Participants will be informed to contact the administrators in the rehabilitation centre in case of any adverse event situation. In addition, participants will be able to discontinue the study once they experience any symptoms of discomfort or adverse event.

### Study assessments

#### Participants’ characteristics

The demographic and health characteristics of subjects will be collected at baseline (Table 1). The characteristics will include age, gender, education, marital status, drug abuse years, type of drug use, whether exercise, weight (kg), height (cm), body mass index, blood pressure (mmHg) and lung capacity (ml). Automatic equipment (Omron sphygmomanometer), electronic digital scales and electronic lung capacity tester will be used to measure blood pressure, weight, height and lung capacity, respectively.

**Table 1 Tab1:** Demographic and characteristics of participants

	HIIT (*n=80*)	MICT (*n=80*)	CON (*n=80*)
Age			
Gender			
Education			
Marital status			
Drug abuse years			
Types of drug use			
Whether exercise			
Weight (kg)			
Height (cm)			
BMI			
Hypertension (mmHg)			
Pulmonary (ml)			

### Primary outcome assessment

#### Stroop test

Stroop is one of the most widely used neurocognitive tasks [63, 67] and as a tool to assess the efficiency of inhibition mechanisms and explore the relationship between inhibition and impulsivity [72]. Individuals with substance use disorders have lower baseline metabolic activity in the prefrontal cortex (PFC), which is associated with impaired cognitive function in decision-making and inhibitory control [4, 11]. The cognitive portion of the Stroop test has been used as a psychometric test to assess cognition as it is related to executive function in decision-making and inhibitory control related to PFC exercise.

The experimental materials are ‘RED’, ‘GREEN’ and ‘BLUE’ characters written in Chinese, and conditions will be classified as congruent and incongruent (Table 2). Congruent condition means that the font colour is in line with its literal meaning, whereas incongruent condition means that the font colour disagree with its literal meaning. Participants will be asked to respond to the colour of the word through the following instructions: press ‘J’ key if the colour of the Chinese character is red, press ‘K’ if it is s green and press ‘L’ if it is blue. Keys ‘J’, ‘K’ and ‘L’ correspond to the index finger, middle finger and ring finger of the right hand, respectively. At the beginning of the experiment, the fixation point ‘+’ will be presented in the centre of the screen for 500 ms, and then the experimental stimulus is presented. Participants will be required to identify the colour of the stimulus on the premise of ensuring correct reflection and then use the right finger to make a response. Stimulus words last for 1000 ms or disappear after pressing the button, and then the next test will start after 500 ms.

**Table 2 Tab2:** Primary outcome of the three groups

	HIIT (*n=80*)			MICT (*n=80*)			CON (*n=80*)		
	Pre	Post	Follow-up	Pre	Post	Follow-up	Pre	Post	Follow-up
**Stroop**									
Congruent accuracy (%)									
Incongruent accuracy (%)									
Mean reaction time (ms)									
Congruent RT (ms)									
Incongruent RT (ms)									
Interference cost (ms)									
**Digit span**									
Number in order (min)									
Number in reverse order (min)									
**Symbol search**									
Symbol searched total									

The whole task will be divided into two parts. The first part has a feedback, whereas the latter part has no feedback. The four stages will comprise 40 trials each in formal trials with a 30-s break in between. The three-colour words will be randomly presented to the participants for 24 times, and the symbols of red, green and blue are presented for 16 times. Each subject will receive a total of 120 tests. Response time and accuracy will be recorded at each stage. These two indicators represent an individual’s inhibition control ability (Fig. 3).

**Fig. 3 Fig3:**
[figure not shown]
Stroop test

#### Wechsler Adult Intelligence Scale-III

The Wechsler Adult Intelligence Scale is the most commonly used test for assessing intelligence in various settings, including clinical practice [92]. Two tests from the Wechsler Adult Intelligence Scale-III [78], namely, digit span and symbol search, will be used to evaluate the following cognitive aspects: attention, working memory, processing speed, executive functions and cognitive flexibility.

##### Digit span

Digit span is a subtest in the Wechsler Adult Intelligence Scale-III that constitutes attention and working memory measures. The examiner pronounces a list of digits at a rate of approximately one digit per second, and the patients are required to repeat the list in the same order immediately. If they succeed, a list that is one digit longer is presented; if they fail, a second list of the same length is presented. If participants are successful on the second list, a list one digit longer is given as before. However, if they also fail on the second list, the test is ended. The length of the digit sequences increases gradually from a sequence of three numbers (e.g. 5, 8, 2) to a sequence with a maximum of nine items (e.g. 7, 1, 3, 9, 4, 2, 5, 6, 8). The span is established as the length of the most extended list recalled correctly.

##### Symbol search

This test evaluates attention, speed of mental processing, short-term visual memory, visual-motor coordination, cognitive flexibility, visual discrimination, psychomotor speed and speed of mental operation. It consists of 60 items. The task is to identify whether the symbols displayed in the target group (left) are present in the hunt group (right) within a specific time limit (120 s).

### Secondary outcome assessment

#### Cognitive function test

CogState battery (CSB), a computerised assessment tool, will be used to examine the different aspects of cognitive function. CSB has been applied to the substance-addicted population [17] with good reliability and validity. The following eight aspects of cognitive function will be examined using this tool: speech learning and memory (International Shopping List Task), processing speed (Detection Task), attention and vigilance (Identification Task), visual learning and memory (One Card Learning Task), working memory (Two Back Task), spatial working memory (Continuous Paired Association Learning Task), problem solving and wrong supervision (Groton Maze Learning Task) and social cognition (Social Emotional Cognition Task). All the tests will be conducted in a quiet room. The questions will be presented to the participants in a fixed order by a computer to reduce distractions, and each test will be scored automatically.

#### Craving Automated Scale for Substances (CAS-S)

The Chinese version of CAS-S will be used to assess the craving level and behaviours of the participants. The scale is a self-rating scale with 15 items. Each item has six points: 0 = never, 1 = hardly, 2 = occasionally, 3 = frequently, 4 = very frequently, and 5 = always. The use of addictive substances will be asked at the end of the questionnaire. This scale has been proven reliable and valid for the measurement of drug-craving, drug-seeking and drug use behaviours [77].

#### Mental health characteristics

Mental health characteristics will be collected by the Symptom Check List 90 (SCL-90), which is a psychosomatic screening scale compiled by Derogatis, Lipman, & Covi [24] that is widely used worldwide [3]. SCL-90 measures 10 kinds of mental symptoms, including somatisation, depression, anxiety, fear, compulsive symptoms and other factors. Each measurement item adopts a five-level grading system: (1) not at all, (2) minimal, (3) moderate, (4) severe and (5) extreme. The checklist will be used to assess how you actually feel ‘now’ or ‘in the last week’.

### Statistical analysis

SPSS 25.0 will be used for statistical analysis. The descriptive outcomes will be displayed as mean ± standard deviation. The *F*-test will be applied to test the continuous variables, and the chi-square test will be used to test the classification variables. For the Stroop test, reaction time (congruent and incongruent) and accuracy (congruent and incongruent) will be analysed using 2 (time points: pre-test vs. post-test) × 3 (groups: HIIT vs. MICT vs. control) repeated-measures ANOVA. Other data will also be analysed using repeated-measures ANOVA. All post hoc tests will be corrected by Bonferroni for multiple comparisons. Intention-to-treat analysis will be used to process the missing data. The linear mixed model method will be applied to analyse all continuous variables with random missing values. The magnitude of the difference between fitness levels will be assessed by Hedges’ *g* [28], and the magnitude will be classified as small (0.2 < ES < 0.5), moderate (0.5 < ES < 0.8) or large (ES > 0.8). The significance level will be set at *p* < 0.05 for all analyses.

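### Nine variables are labelled primary and each is tested at 0.05; the only correction, Bonferroni for post hoc tests, does not control error across them

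*Protocol article*

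**What the plan says.** The primary outcome assessment section of the protocol article covers three instruments. Its Table 2, titled "Primary outcome of the three groups", has nine rows:

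- Stroop (six): congruent accuracy, incongruent accuracy, mean reaction time (RT), congruent RT, incongruent RT and interference cost.
- Digit span (two): forward and reverse.
- Symbol search (one): "Symbol searched total".

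The Statistical analysis section assigns congruent and incongruent RT and accuracy to a "2 (time points: pre-test vs. post-test) × 3 (groups: HIIT vs. MICT vs. control) repeated-measures ANOVA". The remaining variables fall under a general sentence: "Other data will also be analysed using repeated-measures ANOVA". On error control it says two things: "The significance level will be set at *p* < 0.05 for all analyses" and "All post hoc tests will be corrected by Bonferroni for multiple comparisons".

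The Introduction states the hypotheses for cognitive functions in general. HIIT and MICT are each expected to beat control, and HIIT is expected to beat both other arms. The article singles out none of the nine variables and gives no ordering, composite or rule for combining them. The sample size section uses one F-test at an unadjusted alpha of 0.05.

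**The concern.** A post hoc test follows an overall test on the same variable. Correcting the three group pairs within each variable therefore leaves nine overall tests, each run at the full 0.05. Nothing in the article limits how many of these nine chances may be reported as a primary effect. A positive finding on one score out of nine could be presented as the trial's primary result, with an error rate above the level that the reader takes from the stated 0.05.

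**Working it through.** **Inputs from the article.** Nine primary variables (Table 2); level 0.05 per analysis and Bonferroni for post hoc tests (Statistical analysis); three equal groups (Randomisation and blinding); 223 evaluable subjects (Sample size calculation), so about 223/3 ≈ 74 per group. A group-by-time test with two time points is a three-group F-test on change scores, with 2 and 3 × 74 − 3 = 219 degrees of freedom.

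**Input assumed.** The correlation r between the variables, shown as a range. The article states no family-wise error rate, so there is no figure of its own to reproduce.

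**Step 1, independence.** 1 − 0.95^9 = 0.370. This is a ceiling that cannot be reached, because mean RT and interference cost are computed from congruent and incongruent RT. A simulation that builds those two rows from the other two gives 0.33 with no other correlation, 0.30 to 0.31 with moderate correlation and 0.26 with high correlation.

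**Step 2, the stated procedure under a global null.** Simulation with equal correlations and 74 per group: overall F-test at 0.05, then pairwise tests at 0.05/3 = 0.0167 if the F-test rejects.

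| Variables | r | Any false overall test | Any false HIIT-control difference, either direction | Any false difference favouring HIIT over control |
|---|---|---|---|---|
| 1 | – | 5% | 1.6% | 0.8% |
| 9 | 0 | 37% | 13 to 14% | 7% |
| 9 | 0.3 | 33% | 12% | 6% |
| 9 | 0.5 | 28% | 10% | 5% |
| 9 | 0.7 | 21% | 8% | 4% |
| 9 | 0.9 | about 13% | 5% | 2% |

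As a check on the fourth column, dropping the overall test as a gate gives at most 1 − (1 − 0.05/3)^9 = 0.140 under independence.

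**Step 3, narrower counts (independent tests).** The four Stroop scores named in the Statistical analysis section plus digit span and symbol search make seven: 1 − 0.95^7 = 0.30. The four Stroop scores alone: 1 − 0.95^4 = 0.19. One score per instrument: 1 − 0.95^3 = 0.14. The point does not depend on counting all nine rows.

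**The case against.** The strongest objection is that a reader might take 21 to 37% as the type I error of the conclusion that HIIT improves cognition. The article does not support that. The figure counts any overall rejection, including differences that involve only MICT or that go against HIIT. The hypotheses are directional comparisons between arms, and those pass through the Bonferroni step. The relevant figures are then 8 to 13% in either direction and 4 to 7% in favour of HIIT. A false finding that HIIT beats both other arms on the same variable stays under 1%. This objection stands and sets the size of the point.

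Three other strong readings also go too far:

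- **That no time point is fixed.** The Stroop ANOVA is explicitly pre-test against post-test.
- **That testing the follow-up visit adds more error.** The stated Stroop ANOVA omits follow-up. For the other variables, a three-level time factor still gives one group-by-time test each.
- **That the plan lets any one success suffice.** It states no such rule; it only fails to exclude it.

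It can also be said that a separate analysis plan may hold a hierarchy. Silence alone would be no finding. Here, however, the article itself labels nine rows primary, sets one level for all analyses and confines the correction to post hoc tests. A hierarchy elsewhere would have to change that text.

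**Conclusion.** The point holds: the primary family has no error control across variables. Under a global null, at least one false overall group effect among the nine is expected in about 21 to 33% of trials for common correlations of 0.7 down to 0.3. The 37% at independence is out of reach, and 21% is not a floor, since a correlation of 0.9 gives about 13%.

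For HIIT against control after Bonferroni, the corresponding figures are about 8 to 13% in either direction and 4 to 7% in favour of HIIT, for correlations from 0.7 down to near 0. With a single variable they are 1.6% and 0.8%, so having nine raises the risk about five- to nine-fold. In absolute terms it remains well below the figure for any overall rejection.

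These results assume equal correlations, 74 per group and that one significant variable may be reported as a primary effect.

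**What to change.** Before outcome data are analysed, name one primary variable at the post-intervention time point, which the Stroop ANOVA already uses. A single Stroop inhibitory-control score would fit, such as incongruent RT or interference cost; the choice is the sponsor's. Make the remaining variables and the follow-up visit secondary. If all three instruments must stay primary, take one score from each and apply Holm across the three.

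The article reports recruitment as ongoing, so the change was still possible when it was written. It needs revised protocol wording and a registry update. The downside is that the other scores can no longer each support a primary claim.

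A single primary variable keeps the 0.05 level used in the sample size calculation. Holm across three starts at 0.05/3 = 0.0167. If the stated effect size of 0.28 is read as Cohen's f (the article does not name the metric), a three-group F-test at that level has power of about 0.94 with 240 subjects and 0.91 with 216 (240 less 10%). Bonferroni across all nine, at 0.05/9 = 0.0056, would lower these to about 0.89 and 0.84.

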Investigations on MICT and HIIT to improve cognitive function have recently gained much attention. Although a few studies explored the effects of HIIT on drug-dependent animals [47], research on the cognitive effects of HIIT on drug dependents, especially MA dependents, is lacking. The aims of this trial are to (1) determine whether HIIT improves the cognitive function of individuals with MA dependence, (2) determine whether HIIT reduces drug craving and improves the mental health of individuals with MA dependence and (3) compare the cognitive rehabilitation effects of HIIT and MICT on individuals with MA dependence. We hypothesise that (1) HIIT and MICT interventions will be effective in improving the cognitive functions of MA dependents compared with the control group and (2) the effect of HIIT will be better than the other two interventions (i.e. MICT and control).

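### Bonferroni for the three pairwise arm contrasts is valid but needlessly conservative; Holm or a closed test keeps 5% familywise error per outcome and gives more power for HIIT versus MICT

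*Protocol article*

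**What the plan says.** Under Statistical analysis, the Stroop reaction times and accuracies go into a "2 (time points: pre-test vs. post-test) × 3 (groups: HIIT vs. MICT vs. control) repeated-measures ANOVA", and other data are also analysed by repeated-measures ANOVA. The multiplicity rule is one sentence: "All post hoc tests will be corrected by Bonferroni for multiple comparisons". The significance level is p "< 0.05 for all analyses". The family of tests is not defined further. The natural reading is the three pairwise arm contrasts for a given outcome.

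The Introduction hypothesises that both exercise arms will do better than control, and that "the effect of HIIT will be better than the other two interventions (i.e. MICT and control". So HIIT versus MICT is a question the trial sets out to answer.

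Sample size calculation sizes the trial on an F-test only, at alpha "0.05 and power = 0.95, we obtained the required sample size of 223 subjects". It gives no power for any pairwise contrast and no pattern for the three means.

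**The concern.** Bonferroni tests each pair at 0.0167 whatever the other two pairs show. With exactly three arms that is stricter than 5% familywise control requires.

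- **Holm** orders the three p-values and compares them with 0.05/3, 0.05/2 and 0.05, stopping at the first failure. It rejects everything Bonferroni rejects and sometimes more, with no added assumption.
- **A closed test** uses the fact that, with three means, any two pairwise equalities imply that all three are equal. The only intersection hypothesis is therefore the global null. A 2-df group test at 5%, followed by each pair at 5%, controls the familywise error strongly.

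At stake is an avoidable risk of missing a real HIIT-MICT difference, on a contrast for which the protocol shows no power.

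**Working it through.** **Inputs**

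- Effect size: the article used published values "to obtain an effect size of 0.28 through the" t test. It does not say whether 0.28 is f or d.
- Enrolment: "The final average enrolment number with an anticipated 10% attrition rate is 240 (80 in each group". So 80 × 0.9 = 72 evaluable per arm.
- Allocation: "A sequence number will be generated by SPSS 25.0 under the ratio of 1:1:1".
- Assumed, not in the article: two-sided pairwise tests, normal data with common variance, equally spaced means, effects in SDs of the analysed quantity.

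**The plan's own figure.** With noncentrality f²N, f = 0.28, alpha 0.05 and power 0.95, 3 numerator df gives N = 223 exactly. The three-group omnibus test (2 df) gives N = 201, and 201/0.9 = 223.3. Read as d, 0.28 would need 332 per arm in a two-sided two-arm t test (277 one-sided), which cannot lead to 223. Reading 0.28 as f is therefore reasonable, but it is an inference. At f = 0.28 and 3 × 72 = 216, the 2-df F-test has 96% power.

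**HIIT-MICT under equal spacing**

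- For means 2d, d, 0 the SD of the means is d√(2/3). So d = 0.28 × √1.5 = 0.343.
- Noncentrality: 0.343 × √(72/2) = 2.06. Error df: 3 × 72 − 3 = 213.
- Bonferroni: the normal approximation is Φ(2.058 − 2.394) = 36.8%; noncentral t gives 36.3%.
- Unadjusted 5% test, a ceiling for the closed test: Φ(2.058 − 1.960) = 53.9%; noncentral t gives 53.5%.
- Holm and the closed test were simulated (400,000 trials): 46.5% and 53.2%.
- At 74 per arm the three procedures give about 37%, 48% and 55%. At 80 per arm they give about 41%, 52% and 58%.

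**HIIT-MICT power at 72 per arm, by pattern of means**

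| Pattern | Bonferroni | Holm | Closed test |
|---|---|---|---|
| f = 0.28, equal steps | 36% | 47% | 53% |
| HIIT-MICT d = 0.28, equal steps | 23% | 30% | 38% |
| Only HIIT differs, d = 0.28 | 23% | 25% | 30% |
| Only HIIT differs, f = 0.28 | 87% | 90% | 93% |

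The gain over Bonferroni is about 2 to 10 points for Holm and 6 to 17 for the closed test. These figures describe the patterns tried and are not bounds. With HIIT-MICT d = 0.28 and MICT 0.56 SD above control, the figures are 23%, 37% and 39%, so Holm gains about 14 points there.

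**Familywise error at 72 per arm, one outcome (simulated)**

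| Truth | Bonferroni | Holm | Closed test |
|---|---|---|---|
| All three means equal | 4.4% | 4.4% | 5.0% |
| One pair equal (several cases) | 1.7% | 2.4–5.0% | 4.3–5.0% |

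None exceeds 5% beyond simulation error.

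**The case against.** The strongest reply is that a valid, standard, prespecified correction is not a mistake, and that choosing a conservative method is legitimate. That stands. A reader might infer that the analysis is wrong as written, but the documents do not support that. The point is about efficiency.

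A reader might also infer that Bonferroni buys nothing in error control. That is not so. With one truly null pair its actual error is 1.7%, against up to 5.0% for the alternatives. This matters because Table 2 lists nine measures under the primary outcome (six Stroop, two digit span, one symbol search). Suppose one pair is null on all nine and the measures are independent, which is an assumption that overstates both figures if they are positively correlated. The chance of at least one false claim on that pair is then 1 − (1 − 0.05/3)⁹ = 14% under Bonferroni, and at most 1 − 0.95⁹ = 37% under the alternatives. Control across measures needs its own rule, whichever pairwise method is chosen.

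Third, the power figures depend on a pattern of means that the article does not give. That also stands, so the gain is given as a range. It is tempting to call HIIT versus MICT the smallest contrast, but the article ranks no contrast sizes, and under equal spacing HIIT-MICT equals MICT-control.

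Finally, the pairwise shortfall comes mainly from sizing the trial on an omnibus F-test. Agreed: the change reduces the shortfall and does not cure it.

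**Conclusion.** The point holds as an efficiency improvement. For three pairwise contrasts, Bonferroni gives up power that 5% familywise control does not require, including on a hypothesised contrast. With 0.28 as Cohen's f, equal spacing and 72 evaluable per arm, HIIT-MICT power is about 36%, 47% and 53% for Bonferroni, Holm and the closed test. The direction was the same in every pattern tried; the size of the gain depends on the pattern. The alternatives' actual familywise error moves closer to 5%, but not above it, for each outcome. Even the best of these figures under equal spacing is far below the 95% quoted for the F-test, so the change should not be read as giving adequate power for HIIT versus MICT.

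**What to change.** For each outcome and visit, replace Bonferroni with Holm across the three pairwise arm contrasts. This is the minimum change and is never less powerful.

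Alternatively, specify a closed test: a 2-df test of the group effect on change at 5% and, if it is significant, each pair at 5%. The 2-df test must be the group-by-time interaction of the 2 × 3 analysis, or the baseline-adjusted group effect at one visit. It must not be the arm main effect, which averages the pre-test and post-test values. Nor should it be the interaction over all three assessments, which has (3 − 1) × (3 − 1) = 4 df and to which the three-group argument does not apply.

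The cost is a change of wording, and the article says recruitment is ongoing, so it can be made before analysis. The simple Bonferroni simultaneous intervals are lost. If unadjusted 95% intervals are shown beside a closed test, the plan should say that an interval can exclude zero although the group test failed, and that no claim then follows. Multiplicity across the primary measures must be settled separately.
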